#### Secondary outcomes

- Pain intensity is measured by three short questions using a 10-point Visual Analogue Scale (VAS) [26].

- Functional status is assessed by the Roland-Morris Disability-24 Questionnaire (RDQ-24), which has shown to be useful in LBP research [27,28].

- Pain coping is measured with the Pain Coping Inventory Scale (PCI) [29].

- Quality of life is measured with the Dutch translation of the Euroqol instrument [30].

- Cost diaries are used to measure direct (non)-medical costs. The cost diary includes direct health care costs relevant to the treatment of LBP, such as visits to a general practitioner, occupational physician, manual therapist, physical therapist, other exercise therapy or complementary health therapists (e.g. acupuncturist), visits to a medical specialist in orthopaedic surgery, neurology, rheumatology, or rehabilitation medicine, and hospitalization. Direct non-health care costs include homecare and costs for paid and unpaid help due to the disability.

- A process evaluation will be conducted after implementation of the protocol and inclusion of the first 40 cases treated with the multidisciplinary outpatient care program. Quantitative and qualitative data about the applicability, compliance, satisfaction and barriers related to the (implementation of the) protocol will be collected. Patient satisfaction will be measured with the Patient Satisfaction with Occupational Health Services Questionnaire (PSOHQ)[31].

#### Prognostic measures

- Potential work-related psychosocial factors is measured with the job content questionnaire (JCQ)[32].

- Data on workload is measured with the Dutch Musculoskeletal Questionnaire (DMQ)[33].

### Sample size

We assume that a Hazard Ratio (HR) of 2.0 indicates a relevant difference between the multidisciplinary outpatient care group and the UC group. This HR is based on HRs found in comparable studies in primary care [15,19,34]. Another assumption is that 40 percent of the sick listed patients due to chronic low back pain does not return to work during the follow-up period (12 months after randomization). We expect a dropout rate of 10%, based on experiences with comparable research [35,36]. To get a complete data set of 115 patients, 130 patients with chronic LBP who are sick listed will be included (HR = 2, with a power (1-β) of 80% and a significance level of 5%) [37]. Before starting the inclusion of patients, a two-week visitors' waiting room survey has been done at the departments of orthopaedics and neurology at the VU Medical Center Amsterdam. This survey showed that at these two departments the percentage of patients sick listed because of LBP is low (3–4%). Because of this low percentage, four other hospitals are recruited so the recruitment period of 24 months duration is likely acceptable.

### Blinding

Patients, therapists and researchers cannot be blinded for the allocated treatment. Treatment allocation takes place after informed consent and completion of the baseline questionnaire. Most outcome measures are self-reported and consequently cannot be blinded. However, since all questionnaires are sent to the patient by mail, researcher and care providers are not likely to influence the way patients complete the questionnaires. In addition, the reliability regarding the self-reported data on RTW is checked by sick leave data derived from databases of occupational health services. The therapists of the multidisciplinary team (care manager, occupational therapist, physical therapist) are not involved in assessing any of the outcomes.

After randomization all patients receive their own code. A run-up number and the first two letters of the visited hospital compose this code. The research assistant will put all data in the computer by code. Therefore, the analysis of the data by the researcher will be blind.

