#### Randomization

An independent statistic performs randomization, using a computer-generated random-sequence table. The randomization will be performed on patient level. The patients are stratified on 2 important prognostic factors before randomization to prevent an unequal distribution. The first prognostic factor is the duration of sick leave (less than or longer than 3 months). The second prognostic factor is job characteristics ((mainly) physical or mental work demands) [17]. This results in a total of 4 strata. For every stratum, block randomization of 4 allocations will be used to avoid unequal treatment group sizes.

The researcher will prepare for each stratum opaque, sequentially numbered, and sealed coded envelopes, with either a note for the multidisciplinary outpatient care group or a note for the UC group. If a patient meets all criteria he/she will be allocated to one of the four strata. The researcher hands over to the patient the first two envelopes (left over) of that stratum where the patient is asked to pick one of the envelopes, open the envelope and sign the note. After randomization, the researcher/assistant registers information in the database about the patient's employer, occupational physician, general practitioner, and medical specialist. Patients in the multidisciplinary outpatient care group choose one of the 10 physiotherapy practices, in which they will perform the graded activity program. After randomization, the researcher/assistant will make, for patients in the multidisciplinary outpatient care group, an appointment for a visit with the care manager of the multidisciplinary outpatient care program. This appointment will take place within one week after randomization.

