#### 2. Qualitative outcome assessment

Outcome variables related to the implementation of the protocol will be gathered by 1. additional questions about the multidisciplinary outpatient care program for patients in the multidisciplinary outpatient care (MOC) group, which are inserted into the questionnaire at T1; 2. an in-depth interview about the multidisciplinary outpatient care program with the first 30 patients randomized to the MOC group, which is done by telephone at T1. The interview will take approximately one hour; 3. questionnaires, sent to the stakeholders involved (employer/supervisor, patient's own GP and OP, professionals of the multidisciplinary team) at T1; 4. two focus groups for 5 to 7 professionals of the multidisciplinary team (care manager, physical therapist, occupational therapist and medical specialist) organized during the first year of recruitment of patients.

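### The claim that the researcher's analysis will be blind rests on a patient code that hides identity but not treatment arm

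*Protocol article*

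**What the plan says.** The Blinding section opens with the statement "Patients, therapists and researchers cannot be blinded for the allocated treatment". It then describes the coding. Each patient receives a code after randomization: "A run-up number and the first two letters of the visited hospital compose this code". On data entry it says: "The research assistant will put all data in the computer by code". From these two facts it concludes: "Therefore, the analysis of the data by the researcher will be blind".

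Three other sections bear on this:

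- **Randomization.** "The researcher will prepare for each stratum opaque, sequentially numbered, and sealed coded envelopes". At allocation, "The researcher hands over to the patient the first two envelopes (left over) of that stratum"; the patient picks one, opens it and signs the note inside. Afterwards "the researcher/assistant will make, for patients in the multidisciplinary outpatient care group, an appointment for a visit with the care manager".
- **Qualitative outcome assessment.** The data collected include "additional questions about the multidisciplinary outpatient care program for patients in the multidisciplinary outpatient care (MOC) group, which are inserted into the questionnaire at T1".
- **Co-interventions and compliance.** Treatments and co-interventions received in both groups are recorded through the cost diaries and questionnaires.

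**The concern.** The blinding claim is an inference, and the inference does not follow. A pseudonym protects identity. Blinding an analysis means concealing the treatment group, and the article describes nothing that does so.

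Patients and therapists know the allocation and most outcomes are self-reported, so the analysis is the only stage at which the article claims blinding. A reader who accepts the claim will assume that choices made at that stage were made without knowledge of the arm. The main such choice is in the Data analysis section, which allows adjustment for baseline dissimilarities if this is judged necessary. Covariates chosen by someone who knows the arms and can see the outcome could be chosen with an eye to the hazard ratio, even unintentionally. To a lesser degree the same applies to deciding whether a return was full and to work with equal earnings, and whether a later absence counts as a recurrence.

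**Working it through.** No power or test calculation applies. The check sets the sections side by side.

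1. **What the code contains.** A running number and two hospital letters (Blinding). Neither element refers to the treatment group, so the code neither reveals nor conceals the arm. Concealment would need a separate masked group label, and the article describes none. The Data analysis section names the main independent variable simply as treatment, MOC or usual care (UC).

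2. **What the researcher knows before analysis.** The Randomization section has the researcher prepare the envelopes and hand them to the patient, who then opens one and signs the note. The researcher or assistant then books a care-manager visit for MOC patients only. This fits the opening sentence of the Blinding section and does not fit its last one.

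3. **What the data reveal to any analyst.** The 3-month (T1) questionnaire carries an additional block of questions for MOC patients only, and the Blinding section says that all data are entered by code.
 - The planned sample is 130 (Sample size) and allocation is in blocks of 4, so the MOC group has about 130 / 2 = 65 patients. At most about 65 records can carry that block.
 - If the 10% dropout expected in the Sample size section also applied to return of this questionnaire (an assumption), the number would be about 65 × 0.90 = 58.5, or roughly 58.
 - The exact count matters little. If the group variable were relabelled A/B in a file that also held these items, one completed block would show which label is MOC.
 - Treatments received, taken from the cost diaries and questionnaires, point the same way.

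4. **Which analyst decisions are exposed.**

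| Decision | What the article fixes | Exposure in the primary analysis |
|---|---|---|
| Covariate adjustment | Adjust where judged necessary; no list given | Open |
| Full RTW to equal work; recurrence | Rule of 4 weeks without partial or full recurrence; monthly self-reported percentage and reason | Limited |
| Source of sick-leave data | Self-report is used for statistics | None |
| Full compliance with the protocol | Used for the per-protocol comparison only | None |

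**The case against.** Several points on the other side carry weight.

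- **Same person.** The article does not state outright that the person who randomizes also analyses. It uses the same term, the researcher, for both, so that is the plain reading, but it remains an inference. Nor does it say who holds the key between code and patient. The weakness of the code does not depend on this.
- **Separate files.** RTW comes from the monthly calendar, not from the 3-month questionnaire. The MOC-only items could be kept out of the primary file, and such detail may sit in a full protocol or analysis plan that is not shown. That is fair, and the absence of those mechanics is not the point. The point is that the article asserts blindness and attributes it to the code alone.
- **Conduct versus analysis.** The opening sentence of the Blinding section can be read as being about trial conduct and the last as being about analysis. That softens the contradiction, but the code still does not mask the arm.
- **Pseudonymization only.** The sentence may have been meant in this sense. In a section on treatment blinding it will not be read so.

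A reader might also infer more than the documents support:

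- That an unblinded analyst could choose the RTW date where calendar and occupational health records differ. The Primary outcome section settles the source: self-report is used.
- That judging who complied fully could move the primary result. The analyses are by intention to treat, and compliance selects patients only for the per-protocol comparison.
- That UC patients are identified by exclusion because they lack the MOC-only answers. An MOC patient who does not return that questionnaire has the same blank.

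**Conclusion.** The point holds as a claim that the described design does not support. The code masks identity and not arm. The researcher who prepares and hands over the envelopes is by the article's own account not blinded, and the coded data contain items that disclose the arm.

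The consequence is limited. The safeguard is missing mainly for the choice of covariates in the Cox model, and to a lesser degree for classifying full RTW and recurrence under a rule that is already fairly specific. The size of any bias cannot be computed from the documents. Nothing here changes the sample size or the power, or makes the log-rank or Cox test invalid, and it would be wrong to read the point that way.

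The conclusion assumes that the code is the only masking device, as the article's wording implies. If a masked group label or a separate analyst exists in a document not shown, the sentence still needs correcting, because it gives the wrong reason.

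**What to change.** Either make the claim true or withdraw it.

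**To make it true:**

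1. Derive and lock the RTW outcome (date of full return, equal earnings, recurrence) and the covariate list before treatment labels are merged. The list then cannot be driven by baseline differences observed between the groups, so the adjustment rule in the Data analysis section needs matching wording.
2. Run the primary analysis on a file that carries masked A/B labels and excludes the MOC-only items and the treatment-received items. Because the patient picks one of two envelopes, the labels have to be made from the signed notes and not from the random sequence alone, by someone with no part in the analysis.
3. Fix the per-protocol criteria by a prespecified rule and apply it after the primary analysis. Compliance with the MOC program reveals the arm, so this step cannot be done blind.

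**To withdraw it:** delete the sentence and report the analysis as unblinded.

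The first route costs one data-handling step and a few lines of text. The second costs one sentence. Neither changes the sample size, the outcome definition or the planned tests.

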### Co-interventions and compliance

During the intervention period co-interventions are discouraged, but cannot always be avoided. Asking patients and therapists independently about all interventions applied will assess the compliance to the multidisciplinary outpatient care program. Information about all treatments and co-interventions received by the patients in the multidisciplinary outpatient care and UC group, are collected by means of cost-diaries and questionnaires.

### Data analysis

All analyses will be performed at patient level. To examine the success of randomization, descriptive statistics will be used to compare the baseline measurements of the two groups. If necessary, analyses will be adjusted for prognostic dissimilarities. The primary independent variable in the analyses will be the treatment (MOC or UC) to which the patient is allocated. The primary dependent variable is sick leave duration in days until full return to own or equal work. Kaplan Meier analyses (including log rank test) will be used to describe the univariate association between group allocation and the sick leave duration until full RTW. The Cox Proportional hazard model will be used to analyze the HR of the RTW rates in both groups in a multivariate model. Longitudinal random coefficient analyses will be used to assess differences between treatment groups in improvement in all secondary outcome measures. The baseline value of the particular outcome variable will be added to the model in order to correct for possible regression to the mean.

All statistical analyses will be performed according to the intention-to-treat principle, i.e. the patients will remain in the group to which they were randomly allocated at baseline. In order to assess whether protocol deviations have caused bias, the results of the intention-to-treat analyses will be compared to per-protocol analyses. Only those patients who complied fully with the intervention protocol will be included.

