#### Interventions

##### 1. Multidisciplinary outpatient care program (MOC)

Multidisciplinary outpatient care is a case management program consisting of a workplace intervention protocol and a graded activity (GA) program. Two clinical occupational physicians were trained as care managers. The content of the interventions and the role of each member of the multidisciplinary team are described in detail below. The flow of the multidisciplinary outpatient care program is shown in Figure 2.

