##### MOC 3: The Graded Activity Program (GA)

This program is based on the principles of graded activity (GA) as developed by Lindström et al. [21,22] and on the operant (conditioning) model described by Fordyce [23]. It is adjusted to the Dutch situation in the study of Staal et al. 2004 [15]. The program used in this study has been adjusted to the particular study population of the BRIDGE-study. This GA program is provided by 10 regional physiotherapy practices located in Amsterdam or in the surrounding area. These practices have already been trained in the GA program in the context of other research projects [15,24,25]. Prior to the study, all physical therapist have followed a practical training course in the GA program (given by trainers) and were updated on the content of the BRIDGE-study.

The aim of the GA program is restoring occupational function and returning to previous work. Its aim is not pain reduction. The essence of the GA program is to implement an individually graded exercise program, which teaches the patient that it is safe to move while increasing the level of activity. During the GA program the patient has an active role in RTW and the physical therapist acts as a coach and supervisor, using a hands-off approach.

The GA program has two phases: 1. a baseline phase (pain/contingent); 2. a treatment phase (time/contingent). In Table 2 the content of the protocol is described. The entire program consists of maximally 26 sessions. The three baseline sessions have to be done in one week. The maximum duration is 12 weeks. However, the program stops as soon as a lasting return to own or equal work has been established. The session limit will not be communicated to the patient, because it will probably lead to a time lag regarding RTW.

**Table 2 T2:** Steps of the graded activity protocol

**Step**	**Characteristics**	
		The GA program starts within one week after the patient visits the care manager.

Before starting the baseline phase		-The PT performs a history-taking and a physical examination; -The PT gives counseling using the bio-psycho-social model on the development and maintenance and the consequences of pain; -The PT states that it is safe to start the GA program.

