**1 Baseline phase**	**Pain Contingent** Patient may stop at any time if he feels pain or other discomfort Individual training 3 sessions of 1.5 hour	- Baseline consists of 6 fixed and 3 free exercises (simulating work situation); - Aim is to determine the maximal performance for each exercise separately; - According to the results, a start quota (70% of the mean) and the load of each exercise session until the end of the program will be set; - The load of each quota depends on the date of full RTW; - When all quota are set, the PT will send the baseline results and the treatment report to the employee, the employer and the multidisciplinary team.

**2 Treatment phase**	**Time contingent** Pain is not a reason for stopping or altering the program Group training twice a week (4–6 persons) 1 hour per session	- The pre-set quota have to be followed strictly; - The PT accompanies the treatment sessions and evaluates the sessions; - A positive reinforcement will be given by the PT after completion of the quota; - When the date of RTW is within a few weeks, the learned behaviour and management of pain will be discussed. At this point the frequency of the sessions will be decreased to once a week until the patient returns to work; - When the employee fully returns to work or after 26 sessions the protocol will stop. A final communication form will be send to the multidisciplinary team.

		Every three weeks, the PT sends an evaluation form to the multidisciplinary team to report the progress of the treatment protocol.

		When the patient is sick listed because of LBP within 4 weeks after RTW, the GA program will be continued. It will again stop as soon as the patient fully returns to work, or all 26 sessions of the GA program are given.

GA, graded activity; PT, physical therapist; RTW, return to work; LBP, low back pain.

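### The analysis and sample size make no allowance for clustering by provider in the programme arm only, so precision may be overstated

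*Protocol article*

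**What the plan says.** **Unit of randomisation and analysis.** Under Randomization: "The randomization will be performed on patient level". Under Data analysis: "All analyses will be performed at patient level".

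**Methods named under Data analysis.** For the primary outcome, the arms are to be compared on time to return to work by Kaplan-Meier curves with a log-rank test. A regression model follows: "The Cox Proportional hazard model will be used to analyze the HR of the RTW rates in both groups in a multivariate model". For the secondary outcomes, "Longitudinal random coefficient analyses will be used to assess differences between treatment groups in improvement in all secondary outcome measures". No provider, practice or training-group term is mentioned for any of them, and the levels of the random coefficient models are not stated.

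**Delivery of the programme.** In the section on the multidisciplinary programme: "Two clinical occupational physicians were trained as care managers". The workplace intervention section names three trained occupational therapists. In the graded activity section: "This GA program is provided by 10 regional physiotherapy practices located in Amsterdam or in the surrounding area". Table 2 gives the format of the treatment phase as "Group training twice a week", in groups of 4 to 6. Programme patients choose their practice after randomisation (Randomization). Usual-care patients are treated by their own doctors and therapists.

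**Sample size.** Hazard ratio 2.0, power 80%, significance level 5%, 40% without return to work at 12 months and 10% dropout give 115 complete and 130 included patients. No design effect is mentioned.

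**The concern.** This is a partially nested design: one arm is treated by a small set of trial providers and the other is not. If practices, therapists or care managers differ in how quickly their patients return to work, outcomes within the programme arm are positively correlated. A log-rank test and an ordinary Cox model, as named, assume independent patients. In that case the standard error of the treatment effect would be too small, the 5% level would be exceeded and power would fall below 80%. Part of an apparent programme effect, or of its absence, could then reflect the particular providers who took part.

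**Working it through.** **Step 1: reproduce the plan's sample size.** Inputs are from Sample size.

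- Freedman events, two-sided 5%, power 80%, HR 2: (1.960 + 0.842)² × [(1 + 2)/(1 − 2)]² = 7.849 × 9 = 70.6.
- Patients: 70.6 / 0.60 = 117.7, so 118, against 115 stated (within 3%).
- The Schoenfeld formula gives 66 events and 66 / 0.60 = 110, a worse fit.
- Dropout: 115 / 0.9 = 128, against 130 stated.

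The stated figure is thus that of an independent-patient calculation, with no room in it for a design effect.

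**Step 2: cluster sizes.** Blocks of 4 imply 1:1 allocation, so 115 / 2 = 57.5 programme patients are analysed. That is 5.75 per practice, 19.2 per occupational therapist and 28.75 per care manager.

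**Step 3: one-arm design effect at practice level.** The ICC is an assumption, because the article gives none.

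- Programme-arm design effect: DE = 1 + (m − 1) × ICC, with m = 5.75.
- Variance multiplier for the treatment contrast: V = (DE + 1)/2, as only one of two equal arms is clustered.
- Actual two-sided error of the naive test: 2 × [1 − Φ(1.960/√V)].
- Power by Freedman with 115 × 0.60 = 69 events: Φ(√(69/V)/3 − 1.960). At V = 1 this is 79%.

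Example, ICC 0.05: DE = 1 + 4.75 × 0.05 = 1.238; V = 1.119; √V = 1.058.

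| Practice ICC (assumed) | True SE vs naive | Two-sided error | Power | Analysed N to compensate (115 × V) |
|---|---|---|---|---|
| 0 | +0% | 5.0% | 79% | 115 |
| 0.01 | +1.2% | 5.3% | 78.1% | 118 |
| 0.02 | +2.3% | 5.6% | 77.2% | 121 |
| 0.05 | +5.8% | 6.4% | 74.5% | 129 |
| 0.10 | +11.2% | 7.8% | 70.2% | 143 |

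Patients choose their practice, so cluster sizes need not be equal. With an assumed coefficient of variation of cluster size of 0.5, DE = 1 + [(0.5² + 1) × m − 1] × ICC. At ICC 0.05 the SE is then 7.5% larger and the error is 6.8%.

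**Step 4: simulation on the survival scale.** Null log-rank simulation, about 58 per arm, 10 practices in one arm, normal practice effects on the log hazard. The assumed between-practice SD is not the same scale as the ICC above.

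| SD of log hazard between practices (assumed) | Two-sided error |
|---|---|
| 0.1 | about 5% |
| 0.2 | 5.4% |
| 0.3 | 6.2% |
| 0.5 | 8.6% |

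A separate run with 57 per arm gave 5.1%, 5.8%, 6.5% and 8.8%. A variance clustered by practice in the programme arm only brought the error back to about 5%.

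**Step 5: the higher-level providers.** The Step 3 formulas at an assumed ICC of 0.05 give an SE 20.6% larger and error 10.4% for 3 occupational therapists, and 30.1% and 13.2% for 2 care managers. Whether an ICC of that size exists at these levels is unknown, and neither 2 nor 3 clusters allow a between-provider variance to be estimated reliably.

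**The case against.** Several objections are fair, and some limit the point.

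- **Unit of analysis.** Patient-level analysis matches patient-level randomisation and does not by itself rule out a frailty, a robust variance or a further random level. The article is condensed, and the full protocol and SAP are not shown. This stands in part. However, the log-rank test and Cox model are named, they assume independence as named, and the sample size confirms that assumption.
- **Too narrow as a fact.** A reader might infer that the intervals are too narrow and the 5% level is exceeded. The article does not support this. Shared providers permit correlation but do not establish it, and at ICC 0 nothing changes.
- **The care manager's role.** A reader might infer that one of two people fixes the return date for half the programme arm. The case management section says the care manager estimates the duration and may adjust the date at 6 and 12 weeks, while final advice stays with the patient's own occupational physician.
- **Group training.** A reader might infer strong correlation from shared groups. With 65 randomised to the programme, 10 practices, at most 12 weeks of graded activity and 24 months (104 weeks) of recruitment, an even spread gives 65/10 × 12/104 = 0.75 trial patients per practice at any time. Trial patients would rarely share a group.
- **The larger figures.** Error rates of 10% or more arise mainly for the occupational therapists and care managers, under assumed ICCs, where no model can correct them. They should not be quoted as the size of the problem.
- **Target of inference.** If the programme changes nothing for anyone, no provider effect arises from it and the test holds its level (4.9% in simulation at SD 0). The allowance matters when the conclusion is meant to extend beyond these particular providers.

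What remains is a stated analysis with an untested independence assumption in one arm, and a cheap way to test it.

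**Conclusion.** The point holds in a conditional form. Neither the named analyses nor the sample size allows for clustering by provider in the programme arm, so stated precision may be too high. At practice level the likely size is small to moderate: negligible at an ICC up to about 0.02, and about 6% to 8% two-sided error with power of about 74% to 70% at an ICC of 0.05 to 0.10. The simulation is consistent with this.

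These figures rest on assumed ICCs and SDs, 1:1 allocation, 115 analysed patients and, except where stated, practices of equal size. At the level of the occupational therapists and care managers the point is a limit on generalisability rather than a correctable error. The planned patient-level estimate remains usable.

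**What to change.** Keep the patient-level log-rank and Cox analyses as primary and add a partially nested sensitivity analysis:

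- **Cox model:** practice as a cluster in the programme arm only, with each usual-care patient as a separate cluster. Use either a frailty term or a practice-clustered variance with small-sample degrees of freedom.
- **Random coefficient models:** a practice random effect in the programme arm only.
- **Data:** record the practice each programme patient chooses. The Randomization section lists employer, occupational physician, general practitioner and specialist as registered, but not the practice. The care manager's database may hold it, but the article does not say so.
- **Interpretation:** state that, because patients choose the practice, a practice effect may also reflect patient mix.
- **Occupational therapists and care managers:** show results by provider descriptively only, and report the small number of providers as a limit on generalisability.

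The cost is a little more analysis, a slightly wider interval in the sensitivity analysis, and a between-practice variance that 10 practices will estimate imprecisely. No additional patients and no change to the design are needed.

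### The log-rank test is univariate and adjustment depends on observed baseline imbalance, so no analysis is committed to the two factors that stratify the randomisation

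*Protocol article*

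**What the plan says.** In the protocol article, the Randomization section says: "The patients are stratified on 2 important prognostic factors before randomization to prevent an unequal distribution". The factors are sick-leave duration (below or above 3 months) and job demands (mainly physical or mental). "This results in a total of 4 strata", and within them "For every stratum, block randomization of 4 allocations will be used to avoid unequal treatment group sizes".

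The Data analysis section does not mention these strata. It makes four statements that bear on the point:

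- Baseline is compared by arm: "To examine the success of randomization, descriptive statistics will be used to compare the baseline measurements of the two groups".
- The next sentence is the adjustment rule: "If necessary, analyses will be adjusted for prognostic dissimilarities".
- The test is unadjusted: "Kaplan Meier analyses (including log rank test) will be used to describe the univariate association between group allocation" and time to full return to work.
- The hazard ratio comes from a model with unnamed covariates: "The Cox Proportional hazard model will be used to analyze the HR of the RTW rates in both groups in a multivariate model".

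The section does not say what makes adjustment necessary. It also does not say whether the log-rank test, an unadjusted Cox model or an adjusted Cox model gives the primary result.

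**The concern.** The adjustment rule works against the design. Variables used to stratify a blocked randomisation are balanced by construction, so a rule that adjusts for what looks unequal passes over them. It selects other variables that happen to differ, whether or not they predict return to work.

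Two things are at stake. First, if the strata are prognostic and are left out, the standard error takes no credit for the balance that blocking achieved. The test then rejects too rarely under the null and has less power under the alternative. The sample size is set for 80% power, with little to spare. Second, which model is fitted stays open until baseline has been compared by arm, and no threshold limits the choice.

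**Working it through.** **1. The plan's own sample size.** Inputs from the Sample size section: hazard ratio 2.0, power 80%, significance level 5% (taken as two-sided), 40% without return to work at 12 months, dropout 10%, 115 complete and 130 included.

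- Freedman events: (1.960 + 0.842)² × ((2 + 1)/(2 − 1))² = 7.849 × 9 = 70.6. Patients: 70.6/0.60 = 118.
- Schoenfeld events: 4 × 7.849/(ln 2)² = 65.3, rounded up to 66. Patients: 66/0.60 = 110.
- The stated 115 lies between the two. At 115 × 0.60 = 69 events, power is 79.1% (Freedman) or 82.1% (Schoenfeld).
- Dropout: 115/0.9 = 128, against 130 stated.

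The sample size is reproduced closely enough and is not at fault.

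**2. Would the trigger pick a stratification factor?** With blocks of 4, the arms can differ by at most 2 in a stratum. Each level of a factor spans two strata, so the worst case is +4 at one level and −4 at the other. With four equal strata and 57 patients per arm, that is 30 v 26 at one level and 27 v 31 at the other. Chi-square is 0.56, p = 0.45.

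The Randomization section also lets the patient choose between the first two remaining envelopes of the stratum. That can stretch the difference to 3 per stratum, giving 31 v 25 and 26 v 32: chi-square 1.26, p = 0.26. Neither extreme passes p < 0.05 or p < 0.20.

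**3. What would the trigger pick?** Assume five independent, unstratified binary covariates. The chance that at least one triggers is 1 − 0.95⁵ = 23% at p < 0.05 and 1 − 0.80⁵ = 67% at p < 0.20. Simulation gave 22–24% and 66%.

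**4. What does omitting the strata cost?** Simulation: 115 patients, four equal strata, blocks of 4, 40% censored overall at 12 months, true within-stratum hazard ratio 2.0, 6,000 runs per row. The prognostic hazard ratios of the two factors are assumed, because the article gives none.

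| Factor HRs (assumed) | Median HR, unstratified v stratified | Power, unstratified v stratified |
|---|---|---|
| 1 and 1 | 2.00 v 2.00 | 82% v 81% |
| 1.5 and 1.5 | 1.96 v 2.00 | 79% v 81% |
| 2 and 2 | 1.89 v 2.01 | 77% v 82% |
| 3 and 2 | 1.81 v 2.01 | 71% v 82% |
| 3 and 3 | 1.75 v 2.02 | 65% v 81% |

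The Monte Carlo standard error of each power is √(0.8 × 0.2/6000), about 0.5 points. A second simulation with 116 patients gave the same pattern: 82% v 82%, 80% v 82%, 77% v 82% and 66% v 81% for factor hazard ratios of 1, 1.5, 2 and 3 each.

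Under the null, the unstratified test rejects in 4.9% (1.5 each), 3.4% (2 each) and 2.3% (3 each) of runs. The stratified test stays between 4.7% and 5.1%.

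**5. What does the open choice of model cost?** With the five covariates of step 3 at hazard ratios of 1.5 or 2 each, 5,000 null runs per case:

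- Following the rule mechanically gives 4.2–5.0% type I error.
- Reporting the more significant of the adjusted and unadjusted results gives 5.3–6.4%. That is 0.5 to 1.1 points above the unadjusted test in the same runs.

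**The case against.** - **The Cox model may include the strata.** A reader might infer that the Cox analysis ignores the strata and can never adjust for them. The article does not say so. It places the hazard ratio in a multivariate model and leaves the covariates unnamed, and a condensed article may leave that list to an analysis plan that is not shown. This stands, so the missing list is not itself the finding. The univariate log-rank test and the imbalance rule are stated, however, and an analysis plan that followed them would inherit the problem.
- **The hazard ratio need not be diluted.** A reader might infer that the reported ratio will be biased towards 1. That happens only if the reported Cox model omits the strata, and the size rests on assumed prognostic strengths. Part of the shift is non-collapsibility: an unstratified ratio is a valid marginal quantity. The article does not say whether its 2.0 is marginal or within-stratum. If it is marginal, the table overstates the loss. All of this stands.
- **The error is on the safe side.** Omitting the strata makes the test conservative. A reader might infer a serious excess of false positives from the data-dependent choice, but step 5 shows at most a modest one, and only if the better result is selected.
- **There is some protection.** The trigger looks at baseline rather than outcome, and the Blinding section expects the analysis to be blind through coded data. Both narrow the scope for choice. Neither supplies the missing criterion, and the same section says that researchers cannot be blinded to allocation.

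**Conclusion.** The point holds in a limited form. The article states an adjustment rule that has no criterion and, because of blocking, would practically never reach the two factors that the design treats as prognostic. It also fixes an unstratified log-rank test and commits no analysis to those factors.

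If the strata are in fact omitted, the cost is lost power and a conservative test, not false positives. The loss is about 0 points with non-prognostic factors, 2 at factor hazard ratios of 1.5 each, 5 at 2 each and 15 at 3 each. With prognostic factors the estimated ratio moves from 2.0 to 1.96–1.75, partly a marginal-versus-conditional difference. These figures assume equal strata, 60% events overall and a within-stratum ratio of 2.0. The imbalance argument in step 2 also assumes equal strata.

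This should be fixed, but it does not invalidate the trial or its sample size.

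**What to change.** Name one primary analysis: a log-rank test and Cox model stratified by, or adjusted for, sick-leave duration (under or over 3 months) and job demands (physical or mental). Delete the conditional adjustment sentence, or move imbalance-driven adjustment to a sensitivity analysis. Keep the baseline comparison as description. Further covariates are optional and, if used, should be listed before data are compared by arm.

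The change is to wording only. Both factors must be known before randomisation in order to assign the stratum, so nothing new is collected. The statistical price is at most about 1 point of power if the factors prove not to be prognostic (82% v 81%).
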